#### Statistical models to assess whether IC is a predictor of ADLs/IADLs, falls, and death

Two Cox regression models will be evaluated to estimate the incidence rates of outcomes (i.e., functional loss measured by IADLs, falls, and death) associated with IC at baseline (e.g., TIC, DIC, and WIC) (ElHafeez et al., 2021). Cox’s first model has the indicator variable X to denote the association with each of the two groups of IC exposure at baseline (e.g., X1 = 1 for medium and high TIC and X1 = 0 for low TIC), with Y being the adverse incident at 3 years of follow-up (loss of ADLs/IADLs, falls, and death); survival times will be measured by the interval from the first assessment to the adverse incident. For subjects who do not experience an adverse incident, the follow-up time will be the last evaluation of the study.

The model also comprises a collection of covariates V with the potential to be a confounding factor in the association between Y and X (e.g., sociodemographic factors), and W would be the potentially interactive term between X and V (e.g., sex * TIC). The regression coefficient of X describes the effect of TIC on outcome Y, that is, the risk of greater or lesser loss of ADL/IADL, falls, and death for those exposed to medium or high TIC relative to those exposed to low TIC. The W terms will assess whether there is a positive interaction between TIC and one of the V confounders that have been identified to be potentially interacting. The model will extend by substituting TIC for DIC or WIC as the main exposure variable X. Alternatively, we can also model Y (e.g., IADL) as a function of X (either TIC, DIC, or WIC) and the same set of V and W using logistic regression to estimate the odds ratio of the outcomes.

We will evaluate the IC trajectory through changes in IC scores (∆IC or WIC) or the presence of IC decline (DIC) after 3 years, along with their associations with IADL outcomes, falls, and death. For example, the mean/median of ∆IC (or WIC) and the prevalence of DIC will be generated at baseline and at the end of the 3-year follow-up. We will then generate the mean/median or prevalence of IC measure by levels of ADL/IADL, falls, and death. The means/medians of IADLs and the incidence of falls and death after 3 years of follow-up will also be estimated.

In contrast, we should also be able to model Y as ∆IC (ordinal variable with values from 0 to 10) as a function of a main vector X (IADL, falls, or death) and a collection of parameters V and W similar to the previous model, but using a multivariate ordinal regression model with a latent variable specification, where composite probability methods are applied to estimate model parameters (Hirk et al., 2019).

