### Objectives

The cohort study proposed here addresses the determinants of IC and its relationships with FAs that allow longevity with good health and independence in everyday life. Considering that the literature on cohort studies that indicate IC values for the different aging trajectories is limited, we intend to build an IC index composed of the different domains, which can be validated as a risk indicator for classic outcomes such as hospitalization, falls, death, and severe dependence. We also intend to use the data to design clinical trials and nested case–control studies, with sample power, to evaluate measures aimed at preventing or mitigating functional ability losses over time.

To that end, we aim to1. Create a population cohort of people aged 60+ (LONGFUN) living in a middle-class neighborhood in a large urban center in Brazil.2. Create a composite IC index considering the five domains: cognitive, psychological, sensory, locomotor, and vitality.3. Carry out an epidemiological segmentation considering the index composed of IC and the sociodemographic, behavioral, and clinical factors.4. Identify the genetic and immunological biomarkers associated with each segment in a representative subsample of the cohort to be evaluated by a geriatric and multidisciplinary team that will define the needs of care for each segment.5. Analyze the trajectory of the IC composite index for the total cohort and for each segment created, seeking its predictive power as an indicator of risk for the main outcomes: hospitalization, disability, falls, and death.6. Monitor IC changes over time and the impact of the changes on baseline predictors.7. Propose strategies for the development of an integrated system for people-centered healthcare based on the identified needs for care.

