**FIGURE 1 F1:**
[figure not shown]
Proposed study design.

In a period of 6 months, we expect that a team of trained interviewers will contact all potential cohort participants. Based on information from a recent study on the association of IC with the outcome incidence rates of functional dependence, falls, and death (Prince et al., 2021), we developed sample size estimates for comparing two proportions that represent the rates of outcomes in the groups that are exposed (low IC) and unexposed (medium or high IC) (see Tables 1, 2). Calculations considered various effect sizes (relative risk) and incidence or mortality rates. In estimating the sample size needed for this cohort study, this study considered the incidence of the expected outcome in the unexposed cohort (high IC), the risk assumed in the exposed group relative to the risk of the unexposed group (RR), a specific level of confidence (1-α = 0.95; where α = type I error rate), and a specific value of the desired sample power (1-β = 0.80; where β = type II error rate) for the detection of significant differences between the two cohorts. The outcome incidence rate in the cohort was used as a proxy for the expected outcome incidence rate in the unexposed group (high IC). The summary tables (Tables 1, 2 below) provide sample sizes for extremes of the assumed incidence and mortality rate values and the respective relative risks based on the confidence intervals of these measures. A total sample size of approximately 5,500 individuals (assuming 2,750 per group) will be sufficiently robust to maintain the desired power under most diverse scenarios and varying parameters, even if the dropout rate reaches approximately equal to 15% in the two cohorts. The exception will be with very small estimates of the relative risk of death (RR ≤ 1.3).

**TABLE 1 T1:** Sample sizes for specific values of functional loss (FL), incidence, and relative risk for intrinsic capacity (IC) and FL.

	Average risk ratio	Low risk ratio	High risk ratio
Risk ratios (RR)	1.91	1.7	3.0
Incidence rate among the unexposed group	0.0495	0.04925	0.04925
Confidence level (1-α)	0.95	0.95	0.95
Power (1-β)	0.8	0.8	0.8
Study type	Cohort	Cohort	Cohort
Sample per group (n_i_)	514	816	138
Total sample (n_1_+n_2_)	1,028	1,632	276

**TABLE 2 T2:** Sample sizes for specific values of total mortality (TM) and relative risk for IC and TM.

	Average risk ratio	Low risk ratio	High risk ratio
Risk ratios (RR)	1.66	1.3	2.0

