### Explanatory variables: IC composite index (ICI)

An IC composite score or index (IC index or ICI) will first be created, as suggested by Gutiérrez-Robledo et al. (2019). This score aims to express a summary measure of impairments for an older adult. Initially, each continuous or ordinal subdomain measure will be dichotomized based on acceptable cut-off points to create a binary variable of 0 or 1 (see Table 3 for cutoff points across all subdomain measures). Within a domain, the values of these recoded subdomain measures will be summed up to create a “subdomain score.” The subdomain scores will range from 0 to 2 for the four subdomains with only two measures and from 0 to 6 for the subdomain with six measures (i.e., vitality). Then, each domain of the five IC components will be subdivided into three categories based on the sum of the scores of its subdomains, with the following numerical score: no impairment = 0, mild impairment = 1, and severe impairment = 2. For example, the four domains with only two subdomain measures (e.g., cognitive with subdomain measures memory and cognitive) will be coded 0 if their subdomain score (sum of their subdomain measure) is 0, 1 if the subdomain score value is 1, and 2 if the subdomain score value is 2. The domain with six subdomain measures, vitality (subdomains comorbidity, medication, biomarkers, pain, strength, and nutrition), will be coded 0 if its subdomain score is 0, 1 if the subdomain score is 2–4, and 2 if the subdomain score is 5–6. Scores for each of the five domains will be summed up to produce a composite IC index ranging from 0 (best possible ICI) to 14 (worst possible ICI).

Subsequently, this baseline ICI will be classified in four ways. First, using the terciles of ICI (TIC), ICI values less than or equal to the first tercile (Q1) will be classified as low TIC; ICI values between Q1 and the third tercile (Q3), including Q3, will be classified as medium TIC; and ICI values above Q3 will be classified as high TIC. This analysis model is explicitly shown in Figure 1.

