### Generation of weighted IC score (WIC)

To build the weighted IC score (WIC), first, associations between subdomains of IC domains (sensory, mobility, vitality, cognitive, and psychological) and IADL loss will be evaluated by IADL models in a two-stage logistic regression (Meng et al., 2022). For this purpose, IC subdomains will be dichotomized, such as body mass index (BMI) (overweight–obese v. normal–underweight) and handgrip strength (normal–strong v. weak), both of which are subdomains of the vitality domain (Chen et al., 2020). The first stage of modeling requires bivariate analysis between each IC subdomain and IADLs to identify candidate subdomains to enter the multivariate logistic model (Meng et al., 2022). For this, the variable in the model whose *p-*value for the statistical test of association (chi-square) with IADL is less than or equal to α = 0.25 will enter the multivariate logistic regression model with adjustment for the sociodemographic, comorbidity, behavioral, and clinical factors. An exception will be variables selected *a priori* since they are clinically fundamental, such as BMI from the vitality domain.

In the multivariate logistic regression model, subdomains whose *p-*values are less than or equal to α = 0.05 (statistically significant) will be used to generate WIC as follows. For the regression coefficient in the multivariate model that reaches statistical significance (*p ≤* 0.05), its component will be transformed into a subdomain score by dividing the coefficient by the smallest regression coefficient in the model after rounding the absolute value of the coefficient to the nearest integer value. Regression coefficients that are not statistically significant in the adjusted model will have a value of one (1) point. A summary WIC will be obtained by adding points from all regression components. The subdomain terms will enter the multivariate regression model such that the higher the WIC score, the better the IC.

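### The first Cox model cuts the ordered IC index to two tercile groups, and no outcome model names the uncut index that the study aims to validate

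*Protocol article*

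**What the plan says.** The Objectives section sets out to build a composite index and follow it, "seeking its predictive power as an indicator of risk for the main outcomes: hospitalization, disability, falls, and death". The section on the IC composite index gives each of five domains a score: "no impairment = 0, mild impairment = 1, and severe impairment = 2". The domain scores are summed, and the total is then cut at sample terciles into low, medium and high TIC.

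The section on models for ADLs/IADLs, falls and death begins: "Two Cox regression models will be evaluated to estimate the incidence rates of outcomes". For the first model it gives the coding, as an example: "X1 = 1 for medium and high TIC and X1 = 0 for low TIC". It explains the coefficient only as medium or high against low TIC. It then adds: "The model will extend by substituting TIC for DIC or WIC as the main exposure variable X".

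The sample size section rests on a comparison of two proportions with 2,750 per group. It concedes one gap: "The exception will be with very small estimates of the relative risk of death (RR ≤ 1.3").

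**The concern.** The ICI is an ordered score, and the aim is to show that the score predicts outcomes. A two-group indicator tests something narrower: whether one side of a sample-defined cut differs from the other. It ignores any gradient within each side and gives no hazard ratio per point, which is what a reader needs to judge the index as a risk measure.

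The score also has few integer levels, so the tercile boundaries fall on tied values. The groups need not be near one third and two thirds, and neither split matches the 1:1 allocation in the sample size section.

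At stake are the match between aim and analysis and, for weak effects, power. Death at a relative risk of 1.3 is the scenario the plan already says it cannot power.

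**Working it through.** **1. Is the uncut ICI used anywhere as an exposure?** The candidates in the article are:
- TIC: the tercile classes, reduced to 0/1 in the stated model.
- DIC: binary, and a change from baseline, so not a baseline index.
- ΔIC: a change score, modelled as an outcome in the ordinal regression.
- WIC: graded ("the higher the WIC score, the better the IC"), with no cut stated. Its points come from regression coefficients for IADL loss in this cohort. It is a different score, and testing it against IADL is partly circular.

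None of these is the baseline ICI as a score.

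**2. The plan's own figure.** Table 2 gives mortality in the unexposed p0 = 0.04826 and RR 1.3, so p1 = 0.062738. With two-sided α = 0.05 and power 0.80:

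n per group = (1.960 + 0.842)² × [p0(1−p0) + p1(1−p1)] / (p1−p0)² = 7.849 × 0.10473 / 0.014478² = 3,922, as in Table 2.

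With 2,750 per group, z = 0.014478 / √(0.10473/2,750) = 2.346, and power = Φ(2.346 − 1.960) = 65%. After 15% dropout (5,500 × 0.85 = 4,675), z = 2.163 and power is 58%. The plan's concession is right.

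**3. Cost of the cut, normal score.** For a linear effect, cutting at quantile q keeps a fraction φ(c)²/[q(1−q)] of the information.
- Median: 0.3989²/0.25 = 0.637. At N = 5,500 the uncut z is 2.346/√0.637 = 2.940, so power is 84% against 65%, a loss of 19 points.
- Tercile: 0.3636²/0.2222 = 0.595. With one third exposed, the two-group z is 2.168 (58%) and the uncut z is 2.168/√0.595 = 2.811 (80%), a loss of 22 points.

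**4. Cost of the cut, 11-level score.** The assumptions are ICI 0–10, log-odds of death linear in ICI, and slope and intercept set so that the group below the cut has risk 0.04826 and the group above it 1.3 times that. Per-point power is Φ(β√I − 1.960), where I = N Σ w p(1−p)(x − m)², w is the share at each score x, p the risk there, and m the mean of x weighted by w p(1−p). Two-group power uses the formula in step 2 with the actual group sizes. The cut is the score boundary nearest the tercile. N = 4,675.

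| Beta-binomial(10) shape | Worst third vs rest: two-group / per-point | Best third vs rest: two-group / per-point |
|---|---|---|
| (2,5) | 52% / 71% | 53% / 82% |
| (3,7) | 54% / 73% | 49% / 80% |
| (2,3) | 47% / 68% | 54% / 77% |
| (20,50) | 51% / 71% | 58% / 78% |

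The loss is about 19 to 21 points for worst third against the rest, and about 20 to 31 for best third against the rest. A wider set of shapes with a log-linear hazard at N = 5,500 gives similar limits. A uniform score cut above 3 gives 61% against 76% (14 points). A binomial(10, 0.5) score cut above 6, where ties leave only 17% above the cut, gives 38% against 69% (31 points).

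**5. Where the loss is small or reversed.**
- RR 1.66 for death, the average case in Table 2, same four shapes, worst third against the rest, N = 4,675: 97–99% against more than 99%, a loss of about 1 to 3 points.
- Functional loss at RR 1.7 (Table 1, incidence 0.04925), one third exposed, N = 4,675: z = 0.034475/0.00802 = 4.30, so two-group power is already 99%.
- If 0.04826 were an annual rate over the 3 years, two-group power at RR 1.3 would be 90–97% and the loss 3 to 9 points. Table 2 itself uses it as a proportion.
- If risk truly steps at the cut, the linear score is the weaker test, by 12 to 22 points.

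**6. Points that block a per-point ICI as written.**
- The index is described as a "composite IC index ranging from 0 (best possible ICI) to 14 (worst possible ICI"), but five domains scored 0–2 sum to at most 10, and ΔIC is given an upper limit of 10.
- Vitality is coded for sums of 0, 2–4 and 5–6. A sum of 1 has no code.
- ICI 0 is best, so low TIC is the best third, while the sample size section calls low IC the exposed group.

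**The case against.** Four points on the other side carry weight.

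First, a reader might infer that the two-group model is the main analysis and that no graded measure enters a Cox model. The article supports neither. It calls this the first of two models, offers the coding as an example, does not set out the second separately, and refits with the graded WIC. What remains is narrower: the index named in the aim is not itself entered as a score.

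Second, a reader might take the loss as a fixed 18 to 20 points. That range is obtainable, but the documents give neither the score distribution nor the shape of the dose-response, and they conflict on which third is separated.

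Third, a reader might conclude that the gap at RR 1.3 is mostly a product of the coding. It is partly so under linearity. But with worst third against the rest, per-point power after dropout is 68–73%, still short of 80%. In the average mortality scenario and the low-RR functional-loss scenario checked above, two-group power is already high.

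Fourth, a tercile contrast is easy to present, and its cut values can be reported and reused elsewhere. It would therefore be too strong to say the result cannot be carried to another population. This supports keeping the contrast as a secondary presentation.

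**Conclusion.** The concern holds as a mismatch between aim and model. The study sets out to validate the ICI, yet the stated Cox coding reduces it to two groups, and no outcome model names the uncut score. This does not depend on any power figure.

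The power cost depends on assumptions. If log-risk is roughly linear in the ICI and 0.04826 is a proportion over follow-up, it is about 14 to 31 points for death at RR 1.3 (about 19 to 21 for worst third against the rest). It is about 1 to 3 points at RR 1.66, smaller if the rate is annual, and of opposite sign under a true threshold at the cut. The article argues for no such threshold.

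**What to change.** First reconcile three things: the stated ICI range of 0–14 with the 0–10 implied by the domain scoring, the missing code for a vitality sum of 1, and the direction of low TIC against the exposed group in the sample size section.

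Then name the uncut baseline ICI as the prespecified exposure in the Cox models and in any logistic alternative, add a spline or quadratic term to check linearity, and report the hazard ratio per point or per SD. Keep the tercile contrast as a secondary or descriptive presentation, and WIC as a separate score.

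The cost is a few sentences and no new data. The article states that no data have been collected, so the change can still be prespecified. The downside is the linearity assumption: the spline check would reveal a threshold but would not recover the power lost to one. The fix may not reach 80% power at RR 1.3 after dropout, so the stated exception for death should remain.

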In addition, there is a pressing need in healthcare services for studies that assess the impact of effective health promotion strategies—cognitive stimulation, promotion of physical activity, and nutritional education—in preventing IC loss and maintaining FA in elderly people in Brazil. For this purpose, longitudinal observational studies are needed to initially assess these scientific assumptions and justify and guide future studies of controlled interventions.

This paper describes a proposal to 1) constitute a population cohort of elderly people living in a middle-class neighborhood in a large urban center in Brazil and 2) create a single indicator that expresses the trajectory of IC over the years. For this purpose, an assessment of the IC, the FA, and the social capital of the members at baseline and after 3 years will be carried out, establishing an average rate of IC decline, while controlling for the risk and protective factors—genetic, biological, clinical, behavioral, and environmental. The results will be vital for designing future interventional studies that prevent or mitigate functional ability losses associated with age. We intend, through the results from this cohort, to create an inclusive ecosystem of translational innovation in longevity integrated into a national/global innovation system in a continuous process of development and partnerships.

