## Methods

### Study design

The proposed study is a 3-year prospective cohort study of a population of older adults aged 60 years—the onset age designated by the World Health Organization (2015)—or older in the city of São Paulo, Brazil. The result will be a set of biological, social, clinical, and functional data that will allow the study of the progression of IC over time among this population and its associations with ADL, IADL, falls, hospitalization, and death.

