Second, the change in the ICI value during the follow-up time in the cohort will be measured and referred to as “ICI delta” (∆IC). The ∆IC is calculated as the difference between the ICI measured in the last follow-up wave minus the ICI measure at the baseline (variable with values between 0 and 10). Third, we will consider the presence of a decline in IC (DIC) if one or more declines in an IC domain are found from the baseline measure. As an example of IC domain decline in the cognitive dimension, a Montreal Cognitive Assessment (MoCA) score of 22 at follow-up versus 27.0 at baseline is considered a decline and probable “dementia” (Nasreddine et al., 2005). The opposite will be classified as no decline.

Finally, a weighted measure of IC (WIC) will be derived from the multivariate regression result of the association between IC subdomains and IADL loss, which will be adjusted for individual sociodemographic factors (see the Analysis section below for detailed description of WIC).

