The proposed study may suffer the expected limitations of cohort studies, namely, selection bias, including loss of follow-up and misclassification of exposure, as well as confounding during analysis. The proposed design is less prone to suffer from the possible misclassification of outcomes such as ADL/IADL, hospitalization, frequent falls, and death since their measurements are uncontroversial, scientifically tested, and acceptable (Wæhrens et al., 2021; Prinja et al., 2012; Kitcharanant et al., 2020; Rothman and Greenland, 1998).

In a previous 5-year follow-up cohort study with the participation of 1,600 members from the same eligible population described in this proposal, attrition led to the loss of 500 cohort members in 2 years and 1,000 members by the end of the study period (Ramos et al., 2001; D’Orsi et al., 2011). In order to minimize the biggest threat of loss to follow-up, the proposed design will use a three-pronged strategy. First, the project will offer food and transportation vouchers for those cohort members who attend the scheduled evaluations. Second, eligible participants will be informed ahead of time that the results from a comprehensive battery of clinical laboratory exams and cognitive and functional test results will be available free of charge to cohort participants at baseline and follow-up measurement times. Third, a cloud-based data collection platform will keep participants engaged by providing them with regular feedback on data collection, intervention activities, and study results and sending health educational messages through push notifications, phone calls, or text messages twice a month.

It is also possible that measuring factors in the IC domains, such as balance and gait in the mobility domain, may incur measurement errors. To address the misclassification of these exposure factors, our proposed design will use measurement and scales that are acceptable, standardized, and tested for validity (Beyene et al., 2024). Finally, we aim to minimize confounding in the analyses of measures of associations between IC and multiple factors by collecting and incorporating the most relevant contextual and risk factors for both IC and health outcomes in the statistical models.

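### The stated censoring rule credits people lost or dead before year 3 with event-free time nobody observed, or, on its other reading, can give absent survivors no time at all

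*Protocol article*

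**What the plan says.** The section on statistical models for ADLs/IADLs, falls and death sets the time scale: "survival times will be measured by the interval from the first assessment to the adverse incident". For everyone else it says: "For subjects who do not experience an adverse incident, the follow-up time will be the last evaluation of the study". The same two sentences serve all outcomes, and no separate rule covers people lost before the end or people who die without the event being analysed.

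On the schedule, *Study design* says "The proposed study is a 3-year prospective cohort study", and *Rationale* says that "an assessment of the IC, the FA, and the social capital of the members at baseline and after 3 years will be carried out". No interim assessment is named or dated. The section on the IC composite index does define change as "the difference between the ICI measured in the last follow-up wave minus the ICI measure at the baseline", and the *Discussion* speaks of scheduled evaluations in the plural, so an undated interim wave is possible.

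On loss, the sample size section allows about 15% dropout in each group. *Data analysis* says dropout may be unequal between exposure groups. The *Discussion* calls loss to follow-up the biggest threat and reports that in an earlier cohort of 1,600 from the same population "attrition led to the loss of 500 cohort members in 2 years and 1,000 members by the end of the study period". Between assessments it plans educational messages by "push notifications, phone calls, or text messages twice a month", as a retention measure.

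**The concern.** A censoring time should be the last date on which the person was known to be free of the event. The sentence ties it to an evaluation instead, and can be read in two ways.

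- **The study's closing evaluation (literal reading).** A participant who drops out has no recorded functional loss or fall, so counts as event-free for the full 3 years. A participant who dies without functional loss is also a subject without that event, and is credited with time after death.
- **The participant's own last evaluation.** If the only evaluations are baseline and year 3, someone who misses year 3 is censored at time zero and never enters a risk set. If deaths are found without a visit, people who die before year 3 keep their time and their event. Membership of the mortality risk set then depends on the outcome.

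The absolute incidence and mortality rates that the cohort is meant to deliver are at stake under either reading. The IC associations are also at stake if loss differs between the IC groups. The point concerns how people without the event are censored, not how events are dated.

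**Working it through.** **Inputs from the protocol article.** Unexposed functional-loss incidence p0 = 0.0495 and RR 1.91 (Table 1, average column); mortality in the unexposed 0.04826 and RR 1.66 (Table 2); 5,500 participants; 15% dropout; 3 years.

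**Assumptions.** A 20% (exposed) versus 10% (unexposed) split of loss, which keeps the 15% average; loss independent of outcome within group; no functional loss recorded in people who are lost; 0.04826 as an annual mortality risk. The article gives none of these.

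**The plan's own figure.** Table 1 follows from the unpooled two-proportion formula, n = (1.960 + 0.842)² × [p0(1 − p0) + p1(1 − p1)] / (p1 − p0)². With p1 = 0.0495 × 1.91 = 0.0945, this is 7.849 × (0.0470 + 0.0856) / 0.0450² = 513.1, rounded up to the stated 514. The inputs are therefore read as the plan uses them, and the sample size is not in dispute here.

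**Reading A: the study's closing evaluation, functional loss.**

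- People affected: 0.15 × 5,500 = 825. Unobserved time counted as event-free: up to 825 × 3 = 2,475 person-years.
- Observed risk = true risk × (1 − loss). At 15%: 0.0495 × 0.85 = 0.0421, which is 15% too low.
- Observed RR = true RR × (1 − loss in exposed) / (1 − loss in unexposed).
  - Equal 15%: 1.91 × 0.85/0.85 = 1.91, unchanged.
  - 20% versus 10%: 1.91 × 0.80/0.90 = 1.70. For the low-RR column, 1.70 × 0.80/0.90 = 1.51.
- Time credited after death comes on top and is not in these figures.

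**Reading B: own last evaluation, two visits only, all deaths captured.**

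- Hazard h = −ln(1 − 0.04826) = 0.04946 per year. Over 3 years, per person, 0.1379 die and 0.8621 survive.
- Time: total 0.1379/0.04946 = 2.788 years, of which survivors contribute 0.8621 × 3 = 2.586 and decedents 0.202.
- Estimated rate = deaths / [decedents' time + survivors' time × (1 − non-attendance)].

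| Non-attendance | Estimated rate | Relative to truth |
|---|---|---|
| 10% | 0.0545 | 1.10 |
| 15% | 0.0575 | 1.16 |
| 20% | 0.0607 | 1.23 |

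- Equal 15%: a true ratio of 1.00 stays 1.00, and 1.66 becomes 1.65.
- 20% versus 10%: a true ratio of 1.00 becomes 0.0607/0.0545 = 1.11. Solving the Cox partial likelihood for this case also gives 1.11.
- If 0.04826 is a 3-year risk instead, the two results are 1.17 (rate at 15%) and 1.12 (null ratio).

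**Reading B, ADL/IADL loss and falls.** If these are seen only at the year-3 visit, zero time for non-attenders amounts to a complete-case analysis of 5,500 − 825 = 4,675 attenders. Under loss independent of outcome within group, the ratio is not biased.

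**The case against.** The sentence may state only the administrative end of follow-up for people who stay in the study, leaving losses to a full protocol or SAP that is not shown. That reading is possible. But the article chose to state a rule, and words it to cover every subject without an event. Applied as written, it gives the wrong time for people who are lost or die.

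A reader might infer that absent survivors certainly receive zero follow-up. The documents do not establish this: the references to a last wave and to scheduled evaluations leave room for interim visits, and the study-design figure is not shown. With interim waves, own-last-evaluation censoring gives partial time and is close to ordinary practice.

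A reader might also infer that the mortality ratio is certainly inflated. That needs non-attenders' deaths to be captured while surviving non-attenders are lost, and the article describes no tracing of deaths.

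Finally, the earlier cohort's losses (500/1,600 = 31% at 2 years, 1,000/1,600 = 63% at 5 years) might suggest a much larger bias. No 3-year figure is given, the article does not say whether those losses include deaths, and three retention measures are now planned. The article calls unequal dropout possible and gives no size. At its own equal 15%, the ratios hardly move.

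**Conclusion.** The concern holds as a defect in a stated rule. Read literally, the rule adds unobserved event-free time for ADL/IADL loss and falls. Functional-loss risk is about 15% too low at the plan's own dropout with the ratio intact, and a true RR of 1.91 becomes about 1.70 if loss is 20% versus 10%. On the alternative reading, mortality is about 16% too high at 15% non-attendance, and a null ratio becomes about 1.11 at the same split. That holds only with no interim wave and with non-attenders' deaths captured. The absolute-rate errors need no unequal loss; the ratio errors rest on the assumed split.

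The planned multiple imputation addresses missing variable values and does not define follow-up time. This is a should-fix: the rule governs the main Cox models, but a distorted ratio is not certain on the documents.

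**What to change.** Replace the sentence with a rule for each outcome.

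- **Death:** censor at the last date confirmed alive, meaning a visit or an answered contact. A push notification or text that was merely sent does not show that someone is alive. Ascertain deaths and survival in the same way for attenders and non-attenders.
- **ADL/IADL loss and falls:** censor at the last date on which that outcome's status was obtained. Never count time after death as event-free: either censor at death and report a cause-specific hazard, or treat death as a competing event. Both are standard; name the one chosen.
- **Outcomes seen only at the year-3 visit:** the previous rule still gives non-attenders zero time, so say so. Handle that loss with the multiple imputation already planned in *Data analysis*, or with inverse-probability-of-attendance weights from baseline covariates, using a discrete-time or binary model.
- **Schedule:** state whether any interim wave exists and when.

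The cost is wording, a recorded date of last confirmed contact, and a vital-status check at study close. Logging answered contacts is a small new procedure, since the planned messages are outgoing. No extra participants are needed. The article says no data have been collected, so this can be settled now; contact dates not recorded during follow-up are hard to recover later.
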